# Ketogenic diet in the treatment of epilepsy in children under the age of 2 years: study protocol for a randomised controlled trial

**DOI:** 10.1186/s13063-017-1918-3

**Published:** 2017-04-26

**Keywords:** Ketogenic diet, Epilepsy, Randomised controlled trial, Infants

## Abstract

**Background:**

The incidence of epilepsy is greatest in the first 2 years of life, an age group where there is generally a poor prognosis for both seizure control and neurodevelopmental outcome. Early control of seizures can be associated with better developmental outcome but many of the epilepsies presenting in infancy are poorly responsive to antiepileptic medication. The ketogenic diet (KD) is a high-fat, low-carbohydrate diet designed to mimic the effects of starvation on the body. Dietary fat is converted into ketones in the body and used as an energy source by the brain. The KD has been shown to be successful in controlling seizures in many observational studies, and in two randomised controlled trials (RCTs) in older children. However, little evidence is available in the very young.

**Methods/design:**

An open-label RCT where eligible children (age 3 months to 2 years with epilepsy who have failed two antiepileptic drugs (AEDs)) undergo baseline assessment, including medical and seizure history. Participants then start an observation period (7 or 14 days) with documentation of seizure frequency. Randomisation will occur on day 8 or day 15 to receive the KD or a further AED; the allocated treatment will commence on day 15, with instruction and training. A second assessment (4 weeks after start of treatment) will include a clinical review and tolerability questionnaire (modified Hague Scale of Side Effects – for those allocated to the KD group). Assessments will be repeated at 8 weeks after the start of treatment including biochemical investigations, after which, according to patient response, KD (diet group) or AED (standard AED group) will then be continued or changed. Those in the AED group who have failed to achieve seizure control at the 8-week assessment will then be offered KD outside the context of the trial. Those in the KD arm who fail to achieve seizure control will be changed to standard clinical management. All patients will be followed up for 12 months from randomisation for retention, seizure outcome, quality of life and neurodevelopmental status.

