### Study objectives

The primary objective is to assess the effectiveness of the KD compared to AEDs in the treatment of infants with epilepsy aged 3 months to 2 years of age who continue to have seizures despite previous trials of two AEDs. The secondary objectives are to determine tolerability of the KD relative to standard AEDs, adherence to treatment over time, the effect on quality of life and neurobehavioural progress. Further, we aim to estimate whether the presence of medium-chain fatty acids in the context of use of the KD is associated with seizure control.

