The randomisation schedule will be independently generated and held by Sealed Envelope™. Allocations will be released by email to the coordinating centres once the investigator or research nurse has entered eligible participant information into the web-based randomisation service. Participants will be allocated to either the KD or further AED arm using a simple, concealed, randomisation method. Randomisation will aim to achieve 92 in the KD group versus 68 participants in the further AED arm (see calculation in ‘Sample size’ section). An Enrollment Log will be maintained to keep records of the screened and randomised patients at each site. Withdrawn patients will not be replaced and replacement numbers will not be issued. Whilst it will not be possible to blind participants to their treatment allocation, efforts will be made to minimise expectation bias by emphasising in the trial literature that the evidence supporting the KD for seizure control is currently limited.

A second assessment (4 weeks after start of treatment) will include clinical review and a tolerability questionnaire (modified Hague Scale of Side Effects – see Additional file 2). Assessments will be repeated at 8 weeks after the start of treatment including clinical review, administration of the Infant and Toddler Quality of Life Questionnaire, the tolerability questionnaire, and biochemical investigations. After the 8-week assessment, according to patient’s clinical response to treatment with regards seizure outcome and tolerability, the KD (diet group) or AED (standard AED group) will then be continued or changed. Those in the AED group who have failed to achieve seizure control at the 8-week assessment will then be offered the KD outside the context of the trial. Those on the KD who have failed to achieve seizure improvement at the 8-week assessment will continue with medical management, as per clinician decision. All participants will be followed up for 12 months following randomisation for retention, seizure outcome and neurodevelopmental status. See Fig. 1 (Standard Protocol Items: Recommendations for Interventional Trials (SPIRIT) figure: schedule of enrollment, interventions and assessments) and Additional file 3 for the SPIRIT 2013 Checklist (recommended items to address in a clinical trial protocol and related documents).

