### Statistical analysis

Analysis will be done by intention-to-treat. Baseline characteristics of participants in the control and intervention arms will be summarised. The primary outcome will be seizure count in the final 2 weeks of the intervention period and in the baseline assessment period. Data will be analysed using a Poisson mixed model to account for clustering by centre (synonymous with therapist). The randomised allocation will be entered into the model as a fixed effect as will an indicator of time point (baseline or end of study), whilst the centre will be included as a random effect. Analysis of secondary outcomes (those seizure free and responders) will be analysed using random-effects logistic models – centre being the random effects and randomised group a fixed effect. The process outcomes relating to tolerability and medium-chain fatty acids in the KD group will be analysed using random-effects modelling. Therapist effects will be investigated further in supportive analyses [7, 37].

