### Outcomes

The primary outcome will be the number of seizures experienced during weeks 6–8 compared to the number of seizures in the baseline period.

Secondary outcomes will include (at 8 weeks):Number of children seizure freeResponder rate, defined as the number showing more than a 50% improvement in seizure frequency compared to baseline (taken as the mean daily seizure frequency over the observation baseline period immediately preceding the 8-week review)Tolerance to KD as assessed by side effect questionnaire and blood resultsRelationship between medium-chain fatty acids and seizure control

Secondary outcomes will also include (at 12 months):Retention on treatment (the number of participants who remain on the KD, or the prescribed AED, at 12 months)Quality of life (as measured by the Infant Toddler Quality of Life Questionnaire)Neurodevelopmental outcome (as measured by the Vineland Adaptive Behaviour Scales)

Plasma profiles of medium-chain fatty acids will be evaluated at baseline and at 8 weeks. Assessment of mitochondrial function (respiratory-chain enzymes) and enrichment (citrate synthase) will be determined in white cells and platelets. The effect of specific ratios of medium-chain fatty acids, to mimic patient plasma profiles, upon neuronal mitochondrial function/enrichment (biochemical plus electron microscopy studies) will be documented. Additionally, such fatty acid profiles will be studied, with regards to antiepileptic effect, in an established in vitro (hippocampal slice) model.

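### The tolerability objective compares the diet with AEDs, but the article contradicts itself on whether AED children complete the side-effect questionnaire, and it defines the tolerability outcome for the diet alone

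*Protocol article*

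**What the plan says.** Five places in the protocol article bear on tolerability.

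- **Study objectives:** the aim is comparative, to "determine tolerability of the KD relative to standard AEDs".
- **Abstract, Methods/design:** the 4-week assessment includes a "tolerability questionnaire (modified Hague Scale of Side Effects – for those allocated to the KD group".
- **Methods/design, main text:** at week 4, "A second assessment (4 weeks after start of treatment) will include clinical review and a tolerability questionnaire (modified Hague Scale of Side Effects", followed by a pointer to Additional file 2 where the abstract has the restriction to the diet group. The 8-week assessment includes "administration of the Infant and Toddler Quality of Life Questionnaire, the tolerability questionnaire, and biochemical investigations". Neither sentence limits the questionnaire to one arm.
- **Outcomes:** the 8-week secondary outcome is "Tolerance to KD as assessed by side effect questionnaire and blood" results. No AED counterpart is given.
- **Statistical analysis:** "The process outcomes relating to tolerability and medium-chain fatty acids in the KD group will be analysed using random-effects modelling".

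The legend to Fig. 1 has a mark for procedures done in the diet group only. The figure is not shown, so the rows that carry the mark cannot be read.

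**The concern.** A comparative objective needs a measure taken in both arms and an outcome defined as a contrast between them. Here the objective is comparative, the outcome names only the diet, and the two accounts of data collection disagree. A centre that follows the abstract would not give the questionnaire to AED children. A centre that follows the main text would.

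What is at stake is a stated secondary objective. The Discussion section says that the place of the diet in this age group must be settled for safety as well as effectiveness. A side-effect score collected only in the diet arm of an open-label trial has no concurrent comparator. It cannot show whether the diet is tolerated better or worse than a further AED. It could also make the diet look worse simply because only diet families were asked.

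**Working it through.** The point rests on a comparison of sections. Arithmetic enters only in sizing it.

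**Step 1: what the objective needs.** It needs one measure in both arms and a between-arm contrast.

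**Step 2: what each section supplies.**

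| Section | Measured in both arms? | Between-arm contrast? |
|---|---|---|
| Study objectives | Implied | Yes |
| Abstract, Methods/design | No, diet group only | Not stated |
| Methods/design, main text | No restriction stated (weeks 4 and 8) | Not stated |
| Outcomes | Defined for the diet only | No |
| Statistical analysis | Ambiguous | Not stated for tolerability |

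In Statistical analysis, the sentence on seizure freedom and responders names randomised group as a fixed effect. The tolerability sentence says only that random-effects modelling will be used.

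**Step 3: other two-arm data.**

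- Adverse events: the Trial Management Group terms provide for monthly review at each site and for reporting of unexpected events in either arm. This is safety oversight and is not named as the tolerability outcome.
- Retention at 12 months: Outcomes defines it for both the diet and the prescribed AED, but as a separate outcome. Methods/design says that treatment after week 8 continues or changes according to both seizure outcome and tolerability, so retention mixes the two.
- Blood results at 8 weeks: the biochemical investigations in Methods/design carry no arm restriction, so both arms apparently have them. Outcomes ties them to tolerance of the diet, and they do not capture side effects reported by parents.

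**Step 4: size.** The planned numbers come from the Sample size section and reproduce:

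- difference 90 − 62 = 28; mean variance (45² + 50²)/2 = 2262.5
- n per group = 2 × (1.960 + 1.282)² × 2262.5 / 28² = 60.7, so 61
- dropout: 61/0.90 = 67.8, so 68
- diet arm: 68 × [1 + (8 − 1) × 0.05] = 68 × 1.35 = 91.8, so 92
- total: 92 + 68 = 160

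On the abstract's reading, questionnaire data are absent for all 68 AED children. On the main text's reading, none is lost by design.

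**Step 5: what can still be collected.** Trial status reports 29 children randomised, which is 29/160 = 18% of the target. The split by arm is not given. Assuming the planned 92:68 ratio, the expected AED number is 29 × 68/160 = 12.3, about 12. Under simple randomisation the standard deviation is √(29 × 0.425 × 0.575) = 2.7, so a range of about 7 to 18 is plausible. That leaves about 68 − 12 = 56 AED children still to be randomised (range 50 to 61).

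**The case against.** The strongest reply is that the restriction to the diet group appears once, in a parenthesis in the abstract, and that the fuller main text should govern. The main text sets the questionnaire within assessments described for both arms. The sources that would settle the matter, Fig. 1 and Additional file 2, are not visible. In the Statistical analysis sentence, the words about the diet group may qualify only the fatty acids. Data bearing on tolerability also exist in both arms.

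Much of this stands, and it limits the point in three ways.

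- A reader might infer that the comparison cannot be made and that AED questionnaire data will not exist. The documents do not support that. The article is inconsistent and has not settled on diet-only collection, and adverse events, retention and blood results could give an indirect comparison.
- A reader might conclude from Statistical analysis that tolerability will be analysed in the diet arm alone. The sentence is too ambiguous for that.
- A reader might argue that side effects cannot be attributed to the diet because such symptoms are common in these children. The article gives no background frequency, and the point does not need one.

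The reply does not remove the mismatch. If the main text governs, the Outcomes section still defines tolerability for the diet only, and no section clearly states a between-arm tolerability contrast. This is not detail left to a fuller protocol or an analysis plan, because the article itself states both the comparative objective and the restriction that conflicts with it.

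**Conclusion.** The point holds as an internal contradiction affecting one secondary objective. If the abstract is followed, the named questionnaire cannot support the comparison with AEDs, and only indirect two-arm data remain. If the main text is followed, the data would exist, but the outcome definition would still need to be aligned with the objective.

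The size is therefore conditional: questionnaire data from up to 68 AED children at two visits on the first reading, and a wording defect on the second. The article does not show which reading is in use. The correction should be made, and at the reported stage of recruitment most AED children could still be covered.

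**What to change.** Reconcile the Abstract, Study objectives, Methods/design, Outcomes and Statistical analysis sections:

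1. State that the modified Hague questionnaire is completed in both arms at weeks 4 and 8, with diet-only items marked not applicable for AED children.
2. Define the tolerability outcome as a between-arm comparison of the common items, and say in Statistical analysis that the arms are compared. Model detail can stay in the analysis plan.
3. If diet-only collection is intended, either name the two-arm measure that serves the objective or restate the objective as descriptive for the diet.

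The cost of steps 1 and 2 is one extra parent questionnaire at two visits that AED children already attend, plus changes to the outcome wording and the case report form. If collection has so far been diet-only, AED children already past those visits (at most about 12 on the assumed split, range 7 to 18) will have missing questionnaire data, and the report should say so. Step 3 needs wording changes only, but restating the objective gives up the comparison.

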**Discussion:**

The slow rate of recruitment is an ongoing practical issue. There is a limitation to the number of eligible patients compared to what was predicted, mainly due to the nature of this patient group. After a substantial amendment to widen inclusion criteria and reduce the baseline period to 7 days for patients with a high seizure burden, the rate of recruitment steadily increased. A number of operational concerns regarding dietetic time were also highlighted impacting on the recruitment rate. However, the combination of a low dropout rate and the opening of further centres, the trial should successfully meet the final recruitment target. All nine centres are now recruiting and we hope to open further centres within the UK.

**Trial registration:**

ClinicalTrials.gov, identifier: NCT02205931. Registered on 16 December 2013.

**Electronic supplementary material:**

The online version of this article (doi:10.1186/s13063-017-1918-3) contains supplementary material, which is available to authorized users.

## Background

Epilepsy is a condition whereby individuals are prone to recurrent epileptic seizures, a change in behaviour or movement that is the direct result of a primary change in the electrical activity in the brain. It is not a single condition – there are many different underlying causes and, more accurately, they should be referred to as the epilepsies. Up to 65% of individuals with epilepsy will have seizures controlled with antiepileptic drugs (AEDs) or enter spontaneous remission in their lifetime [1]. However, this leaves 35% who will continue with seizures despite treatment. Standard first-line management of an individual presenting with epilepsy is antiepileptic medication, decided on the basis of the type of epilepsy. Although guidelines exist on which drug to use, management is still based on a ‘trial and error’ approach [2]. When the type of epilepsy or seizure is unclear, it can be difficult to optimise treatment at the outset.

The incidence of epilepsy is greatest in the first 2 years of life (56–88/100,000 children/year), [3] a population who remain most at risk for neurodevelopmental compromise in the longer term. Early control of seizures is associated with better developmental outcome [4] but, unfortunately, many of the epilepsies presenting in infancy are associated with a poor prognosis for seizure control [5, 6]. Little evidence is available with regard to effective treatments and, even where seizure freedom is achieved, this is unlikely to be sustained long term [7]. This group of children place a large burden on health services, with a need for regular clinical review and ongoing medication, as well as clinical and therapy support. This is especially true for those who remain resistant to medication, this group being amongst the most costly for medical and care services long term. It is, therefore, imperative that all other treatment options are explored as early as possible [8].

The epilepsies in this age group also remain poorly defined entities; very few can be classified into an epilepsy syndrome and diagnosis of underlying cause remains difficult. Over 50% of infants presenting with seizures will have infantile spasms [3]. This affects approximately 1 in 2000 infants. First-line treatment options (corticosteroids or vigabatrin) lead to seizure freedom in up to 70% of cases [9] but side effects limit their duration of use and relapse rates are substantial (40%) [10]. Further, those who fail these treatments are limited in their treatment options. Of the remaining types of epilepsy, the majority are resistant to medication. There is little evidence on which to base our decisions on specific AED use in this young age group. Epidemiological data have shown this group to be the least likely to achieve longer-term remission of up to 2 years [11].

The ketogenic diet (KD) is a high-fat, low-carbohydrate diet designed to mimic the effects of starvation on the body. The main energy intake is fat, which is converted to ketones in the body and used as an energy source. The classical KD is based on an intake of long-chain fat, usually in a ratio of 3 or 4 g of fat to 1 g of carbohydrate and protein. The medium-chain triglyceride (MCT) KD utilises MCT fat, which generates more ketones per calorie compared to long-chain fat, theoretically allowing greater dietary intake of carbohydrate. More liberal diets have also been utilised, including the Modified Atkins Diet and low-glycaemic-index treatment, which are high in fat, low in carbohydrate but with unlimited protein [12, 13].

The KD has been shown to be successful in controlling seizures in many observational studies [14, 15]. However, there is limited evidence examining efficacy against no change or alternative treatments from randomised controlled trials (RCTs) [16]. The first RCT of the KD to demonstrate effectiveness in children aged 2–16 years was published in 2008 [17]. In this trial, 145 children aged 2–16 years, who had failed at least two AEDs and had at least seven seizures weekly, were randomised to receive a KD, either immediately or after a 3-month delay with no additional treatment changes (the latter being the control group). After 3 months, the mean percentage of baseline seizures (on an intention-to-treat analysis) was significantly lower in the diet group (62%) than in controls (137%, *p* < 0.0001). Twenty-eight (38%) of the diet group had greater than 50% seizure reduction, compared to four (6%) controls (*p* < 0.0001). One further RCT of similar design and in the same age group has been reported demonstrating efficacy of the Modified Atkins Diet to a similar degree [13]. There has been no RCT assessing treatment with the KD in children under the age of 2 years.

Open-label, observational evidence indicates that the KD could be particularly effective in younger children. Open-label studies have suggested it to be an effective and well-tolerated treatment for infants [12, 18–26]. One study reported significant improvements in infantile spasms and fewer side effects when the diet was used as an alternative first-line therapy to adrenocorticotrophic hormone (ACTH) [27].

The mechanism of action of the KD is not yet known. Recent evidence suggests that medium-chain fatty acids, more specifically decanoic acid, may have a specific role in its antiepileptic effect [28–30]. These data raise the possibility that C10 alone has the ability to mimic aspects of the KD. Whether this has a role in a possibly enhanced action of the KD in infancy should be determined and the biochemical basis for effectiveness identified [31, 32].

The KD is a high-resource treatment, requiring patient-specific calculation and regular input from a specialist paediatrician and dietitian, with close monitoring thereafter. It also requires diligence on the part of the families. It is also not without side effects. It is imperative that the effectiveness and safety of the KD in this very young age group is now studied in a well-designed clinical trial.

### Study objectives

The primary objective is to assess the effectiveness of the KD compared to AEDs in the treatment of infants with epilepsy aged 3 months to 2 years of age who continue to have seizures despite previous trials of two AEDs. The secondary objectives are to determine tolerability of the KD relative to standard AEDs, adherence to treatment over time, the effect on quality of life and neurobehavioural progress. Further, we aim to estimate whether the presence of medium-chain fatty acids in the context of use of the KD is associated with seizure control.

